### Sample size estimate

Based on preliminary power analyses (see below), we plan a 36-month intervention period that includes a 90-day run-in period. Patients intubated during the run-in period will not be included in the final analysis. Estimated enrollment in the final analysis is up to 9900 mechanically ventilated patients over 33 months. Study duration and enrollment targets may be adjusted prior to the intervention period based on C-SAT/SBT adherence and other data observed during the pre-intervention baseline period.

### Type I error control and power analysis

It is questionable to attribute any observed reduction in ventilator-free days in the TEACH treatment arm to the intervention if a significant TEACH effect on adherence is not observed. Therefore, a formal hypothesis test of a TEACH treatment effect on the ventilator-free days outcome will be carried out, with type I error of 0.05, if and only if the TEACH effect on adherence is significant at the 0.05 level. This approach limits type I error to 0.05 for assessment of both outcomes.

### Adherence outcome power

For power estimation, we simulated intervention data using observed adherence proportions at each center during the baseline period, assuming fourfold improvement from baseline in relative adherence odds in the control arm in years 2–4, with higher improvement in the TEACH arm.

Study adherence data will exhibit clustering at the patient and hospital level and possibly by calendar day. We used a partially heuristic approach to power estimation, incorporating the variance inflation factor for clustered studies. Considering the intraclass correlation observed in the baseline study data and the distributions of eligible ICU days per study patient, a heuristic, conservative derivation yields a variance inflation factor of approximately 4.5 for adherence data [62] indicating effective sample size for power estimation can be estimated as actual number of eligible patient days divided by 4.5. Under these assumptions, and conservatively estimating sites’ patient volume for the three study years using 2019 levels incremented by 4% per year, estimated power to detect a significant TEACH effect on adherence is 86.4% if TEACH increases site adherence odds at least 1.333-fold versus control, exemplified by control-arm adherence increase from 40 to 72.7% versus TEACH-arm increase from 40 to 78.0%. Estimated power is 95.4% if the TEACH-related odds ratio is 1.4, exemplified by a site’s adherence increasing from 40 to 72.7% in the control arm versus 40 to 78.9% in the TEACH arm.

### Power for effectiveness outcomes

Power estimations simplistically assume the TEACH intervention will improve ventilator-free days among some percentage of surviving patients within an institution who would have been extubated within 28 days by a single day, compared to baseline-phase ventilator-free days at that same center. We assume no TEACH-related improvement in mortality rates or proportion of patients not extubated by day 27. At control sites, we assume no improvement in ventilator-free day distributions from baseline levels.

Simulations were carried out using final baseline data (with simulated post-intervention data obtained by resampling from each institution’s baseline cohort and then modifying ventilator-free days when appropriate due to modelled TEACH effect) and projected enrollment numbers for the 3 years of the intervention phase. Conservatively, a level of ventilator-free day “granularity” achieving satisfactory model convergence in effectively 100% of simulations was used. From these simulations, estimated power to detect a significant TEACH effect is approximately 87% if TEACH improves ventilator-free days by 1 day (compared to the usual care intervention) among two-thirds of surviving patients ventilator-free within 28 days of intubation. Estimated power is reduced to 51% if this one ventilator-free day improvement occurs among only one-half of such surviving patients.

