### Primary quantitative analysis approaches

Reflecting the cluster-randomized design of TEACH, the primary analysis of treatment effect on adherence will use assigned treatment as a predictor in a logistic mixed-effects model with each observation of adherence as the outcome [59], with appropriate random effect terms including center, patient (nested within center), and calendar day (again nested within center) to model between-observation covariance. Models will also include each center’s baseline pre-C-SAT/SBT-implementation data available during the 6-month baseline period; this substantially improves power to detect a treatment effect, as baseline adherence substantially varies between hospitals. Treatment effect significance will be assessed using a one-sided Wald-type test with type I error of 0.05. To assess robustness of the primary analysis and provide a prespecified “backup” analytic approach if there are tractability issues, a model excluding calendar day effect, and a model fit using generalized estimating equations, are prespecified supportive analytic approaches.

The co-primary ventilator-free days outcome will have a highly skewed distribution, due to a high proportion of deaths, and appreciable proportions of surviving patients with 0 ventilator-free days, or ventilator-free days at or near the maximum possible value of 27. The primary analysis approach for the ventilator-free day outcome is effectively an adjusted rank-based analysis, implementing a proportional odds model including center as a random effect [60], including baseline as well as intervention ventilator-free days as outcomes, and adjusting for covariates including patient age, Charlson Comorbidity Index, PaO_2_/FiO_2_ ratio, and COVID-19 diagnosis [61]. Fitting this model for the ventilator-free day outcome at a granularity level achieving satisfactory convergence (selected in a prespecified fashion independent of treatment effect), a likelihood ratio test with type I error of 0.05 will assess significance of the TEACH intervention by comparing deviance of the model with three levels of treatment (baseline, control, and TEACH) to the corresponding model with treatment modeled as baseline versus intervention only.

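### The 87% and 51% ventilator-free-day powers are stand-alone figures; behind the adherence gate, the chance of a formal finding is about 75% to 83% and 44% to 49% if the tests are independent

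*Protocol article*

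**What the plan says.** Under *Type I error control and power analysis*, the protocol article orders the two co-primary tests. Ventilator-free days are formally tested "if and only if the TEACH effect on adherence is significant at the 0.05 level".

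*Adherence outcome power* reports that "estimated power to detect a significant TEACH effect on adherence is 86.4" per cent at an odds ratio of at least 1.333, and gives 95.4% at 1.4. Site volumes there are projected over three study years.

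*Power for effectiveness outcomes* describes "simulated post-intervention data obtained by resampling from each institution’s baseline cohort", after which ventilator-free days are modified for the assumed effect. The enrolment used is "projected enrollment numbers for the 3 years of the intervention phase". The result is that "estimated power to detect a significant TEACH effect is approximately 87" per cent if two-thirds of the survivors who come off the ventilator by day 28 gain one day. It continues: "Estimated power is reduced to 51% if this one ventilator-free day improvement occurs among only one-half of such surviving patients". The section does not mention the gate.

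*Sample size estimate* sets a 36-month intervention period that contains a 90-day run-in. It states: "Patients intubated during the run-in period will not be included in the final analysis". That leaves up to 9900 patients over 33 months.

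**The concern.** A significant ventilator-free-day result requires two events: adherence reaches significance, and then ventilator-free days do. Its probability is the joint probability of both. The article reports the probability of the second event as though the test were always run.

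*Trial overview and design* gives effectiveness and implementation outcomes equal weight, so this is the power of a co-primary outcome. *Sample size estimate* allows duration and enrolment to be changed before the intervention period. A figure that leaves out the gate makes the planned size look more comfortable for effectiveness than the stated procedure implies. The three-year wording may add a smaller overstatement in the same direction.

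**Working it through.** **What can be reproduced.** The 87% and 51% come from resampled baseline data that the article does not give, so they cannot be recomputed and are taken as stated. The surrounding figures do check. A fourfold rise in odds from 40% gives 72.7%, and further odds ratios of 1.333 and 1.4 give 78.0% and 78.9%, as stated. The annual volume of about 3600 in *Setting* gives 3600 × 33/12 = 9900, as stated; 36 months would give 3600 × 36/12 = 10,800.

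**Step 1: apply the gate.** Let *a* be the adherence power and *v* the stand-alone ventilator-free-day power.
- Under independence, gated power = *a* × *v*.
- Whatever the dependence, it lies between *a* + *v* − 1 and the smaller of *a* and *v*.
- For correlated test statistics, a bivariate normal with correlation 0.3 to 0.8 was used. The correlation is an assumption; the article gives none.

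| Share gaining a day | Stated *v* | Adherence OR (*a*) | Independent | Correlation 0.3 to 0.8 | Bounds |
|---|---|---|---|---|---|
| Two-thirds | 87% | 1.333 (86.4%) | 0.864 × 0.87 = 75.2% | 76.8% to 81.3% | 73.4% to 86.4% |
| Two-thirds | 87% | 1.4 (95.4%) | 0.954 × 0.87 = 83.0% | 83.8% to 86.1% | 82.4% to 87.0% |
| One-half | 51% | 1.333 (86.4%) | 0.864 × 0.51 = 44.1% | 46.7% to 50.6% | 37.4% to 51.0% |
| One-half | 51% | 1.4 (95.4%) | 0.954 × 0.51 = 48.7% | 49.8% to 51.0% | 46.4% to 51.0% |

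**Step 2: the run-in, if 36 months were simulated.** Each power is converted to a noncentrality, multiplied by √(33/36) = 0.957, and converted back: Φ[(z_α + z_power) × 0.957 − z_α]. Adherence has a one-sided Wald test at 0.05, so z_α = 1.645. For ventilator-free days, "a likelihood ratio test with type I error of 0.05 will assess significance of the TEACH intervention". It compares a three-level with a two-level treatment term, which is one degree of freedom and in effect two-sided, so z_α = 1.960.
- Ventilator-free days, two-thirds: Φ(3.086 × 0.957 − 1.960) = 84.0%, down from 87%.
- Ventilator-free days, one-half: 47.6%, down from 51%.
- Adherence, OR 1.333: Φ(2.743 × 0.957 − 1.645) = 83.7%, down from 86.4%.
- Adherence, OR 1.4: 93.9%, down from 95.4%.

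This scaling gives the most that the run-in could cost on this approximation, because the baseline data in the model and the between-center variance do not shrink when run-in patients are dropped.

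**Step 3: gate and 33 months for both tests, independent.**
- Two-thirds: 0.840 × 0.837 = 70.3% at OR 1.333, and 0.840 × 0.939 = 78.9% at OR 1.4.
- One-half: 0.476 × 0.837 ≈ 40% at OR 1.333, and 0.476 × 0.939 ≈ 45% at OR 1.4.

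The two interim looks were not modelled; *Early stopping rules and contingency plan* calls their effect on power minor.

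**The case against.** The strongest reply is that 87% and 51% are per-test powers, given under a separate heading for each outcome, with the gate disclosed shortly before. Reporting marginal power for each step of a gated sequence is legitimate, and type I error control is unaffected. That stands as far as it goes: the figures remain informative and should be kept. But the text does not label them as conditional on reaching the test, and it gives no gated figure.

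Four stronger readings are tempting, and the documents do not support them.
- *The true power is 70% to 75%.* That needs the lower adherence odds ratio and independence, and its 70% end also needs run-in patients in the simulation. The article links neither ventilator-free-day scenario to an adherence odds ratio. Its own 1.4 scenario gives 79% to 83%, and positive correlation, which is plausible if better adherence is what shortens ventilation, raises every figure.
- *The procedure cannot deliver 87%.* At odds ratio 1.4 the upper bound is 87%. The loss shrinks as adherence success becomes near certain or as the two results almost always coincide.
- *The 87% and 51% are miscalculated.* They cannot be checked without the baseline data, and nothing shows them to be wrong as stand-alone powers.
- *The simulations included the run-in.* The three-year wording suggests it, because the intervention period is defined as 36 months. It may instead simply name the phase, and the 9900 in *Sample size estimate* already leaves the run-in out.

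**Conclusion.** The point holds as a mismatch between the stated power and the stated testing procedure. The direction is certain: gated power can never exceed the stand-alone figure, and at adherence odds ratio 1.333 it is below 87% under any dependence. The size rests on assumptions. With the article's own adherence powers and independence, 87% becomes about 75% or 83%, and 51% becomes about 44% or 49%, at odds ratios 1.333 and 1.4. In the two-thirds scenario at odds ratio 1.333, the risk of no formal effectiveness finding is then about 25%, against the 13% that the stated figure implies.

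The enrolment wording is a secondary matter. It needs reconciling, and is worth at most about 3 points per test. No test, alpha level or sample size is shown to be wrong.

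**What to change.** 1. Label 87% and 51% as stand-alone power of the ventilator-free-day test, and keep them.
2. Re-run the simulations with adherence and ventilator-free days generated together, apply the adherence gate, and report gated power for each ventilator-free-day scenario at each adherence odds ratio. Give those figures as the power for the effectiveness co-primary, with the assumed link between the two outcomes.
3. Use 33 months of analysable enrolment for both outcomes, and state in both power sections that the run-in is excluded. If it was already excluded, one sentence saying so is enough.

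The cost is a re-run of existing simulations and a somewhat less favourable stated power. The testing procedure does not change.

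### The two ventilator-free-day power figures lie further apart than a calibrated test allows, and the power work, as worded, counts run-in patients who will not be analysed

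*Protocol article*

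**What the plan says.** **VFD power** (Protocol article, Power for effectiveness outcomes). The assumed effect is a one-day gain in some percentage of survivors who would have been extubated within 28 days. Mortality, the share not extubated by day 27, and control-site VFDs are unchanged. The article states that "estimated power to detect a significant TEACH effect is approximately 87% if TEACH improves ventilator-free days by 1 day" among two-thirds of such survivors, and then: "Estimated power is reduced to 51% if this one ventilator-free day improvement occurs among only one-half of such surviving patients". Both are simulation results. Post-intervention data were resampled from each hospital's own baseline cohort, using "projected enrollment numbers for the 3 years of the intervention phase".

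**VFD test** (Primary quantitative analysis approaches). The plan is a rank-type analysis "implementing a proportional odds model including center as a random effect", with baseline VFDs entering as outcomes alongside intervention VFDs. Then "a likelihood ratio test with type I error of 0.05 will assess significance of the TEACH intervention", comparing a three-level with a two-level treatment factor. That is one degree of freedom, so the test is in effect two-sided.

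**Enrolment.** Adherence power is based on "patient volume for the three study years using 2019 levels incremented by 4% per year" (Adherence outcome power). The Sample size estimate section plans 36 months including a 90-day run-in and says: "Patients intubated during the run-in period will not be included in the final analysis". That leaves up to 9900 patients over 33 months.

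**The concern.** If the improved patients are a random share of the eligible survivors, the TEACH-arm distribution is a mixture whose distance from control is proportional to that share. Going from two-thirds to one-half should then multiply the expected test statistic by 0.75. A fall from 87% to 51% is steeper than that.

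The enrolment wording is a separate matter. Both power sections speak of three years, although the first three months of the intervention period contribute no analysed patients.

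The 87% is the only favourable power stated for this co-primary outcome. Readers and the DSMB will use it to judge whether a null VFD result is informative, and a true value nearer 75% would change that reading.

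**Working it through.** **What can be reproduced.** The absolute VFD powers cannot be rebuilt, because the baseline distribution, hospital sizes, granularity and number of replicates are not printed. The pair can be tested. The adherence section's worked percentages do reproduce: odds at 40% are 0.667; times 4 gives 2.667 (72.7%); times a further 1.333 gives 78.0%; times 1.4 gives 78.9%.

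**1. The pair under a calibrated test.**
- Two-sided 5% critical value: 1.960.
- Mean Z implied by 87%: 1.960 + 1.126 = 3.086.
- Mean Z implied by 51%: 1.960 + 0.025 = 1.985.
- Implied ratio: 1.985/3.086 = 0.643. Expected ratio: (1/2)/(2/3) = 0.75.
- If 87% is right, one-half gives Φ(0.75 × 3.086 − 1.960) = 63.9%.
- If 51% is right, two-thirds gives Φ(1.985/0.75 − 1.960) = 75.4%.
- Read as one-sided 0.05, the same steps give 66.8% and 72.0%, so the gap does not close.

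Coarser outcome categories do not explain it. Expected-count proportional odds fits over five assumed VFD distributions and three granularities gave noncentrality ratios of 0.558 to 0.562, against 0.75² = 0.5625. Enrolment does not explain it either, since both figures use the same enrolment.

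**2. Could the described simulation print both?** The formula above takes SD(Z) = 1 across replicates. If one observed baseline cohort is kept in every replicate, its sampling error is in the model's standard error but does not vary between replicates, so SD(Z) = s is below 1. Then mean Z at two-thirds is m = 1.960 + 1.126s, and power at one-half is Φ((0.75m − 1.960)/s).

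| s | Power at two-thirds | Power at one-half |
|---|---|---|
| 1.0 | 87% | 63.9% |
| 0.8 | 87% | 59.2% |
| 0.7 | 87% | 55.8% |
| 0.6 | 87% | 51.1% |

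An illustrative Monte Carlo check used 250 runs per setting, 12 hospitals, 1800 baseline and 10,800 later patients, and a rank-score mixed model standing in for the proportional odds model. The VFD distributions, hospital shares and between-hospital SD were assumed. With fixed baseline, SD(Z) was 0.53 to 0.87, pairs included 82%/49% and 85%/58%, and null rejection was 0 to 2.4%. With redrawn baseline, SD(Z) was about 1 or more (0.96 to 1.55) and null rejection was 4% to 16%. So the printed pair is attainable with a fixed baseline.

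**3. What a fixed baseline would mean for the 87%.** With s = 0.6, m = 1.960 + 0.6 × 1.126 = 2.636. Restoring SD(Z) = 1:
- two-thirds: Φ(2.636 − 1.960) = 75.0%;
- one-half: Φ(0.75 × 2.636 − 1.960) = 50.7%.

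The simulated null rejection rate would be 2 × (1 − Φ(1.960/0.6)) ≈ 0.1%, against a nominal 5%.

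**4. Replicate noise.** With 100 independent replicates per setting, the standard errors are 3.4 points (at 87%) and 5.0 points (at 51%). Near 87%, one point there moves the predicted one-half power by about 1.33 points (86.5% gives 63.2%, 87.5% gives 64.5%). The standard error of the discrepancy is √((1.33 × 3.4)² + 5.0²) ≈ 6.7 points. The observed 12.9 points is then about 1.9 standard errors. With 500 replicates (standard errors 1.5 and 2.2) it is about 4.3. Noise matters only if replicates were very few.

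**5. Run-in.** At the article's rough 3600 patients a year, 3600 × 2.75 = 9900, which matches the stated analysis set, while 3600 × 3 = 10,800, about 9% more. Two limits for the effect on mean Z:
- precision driven by intervention-period numbers: √(33/36) = 0.957;
- change from a six-month baseline: √[(1/6 + 1/36)/(1/6 + 1/33)] = 0.994.

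| Stated power | Factor 0.957 | Factor 0.994 |
|---|---|---|
| VFD 87% | 84.0% | 86.6% |
| VFD 51% | 47.6% | 50.5% |
| Adherence 86.4% (one-sided 0.05) | 83.7% | not computed |
| Adherence 95.4% (one-sided 0.05) | 93.9% | not computed |

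**The case against.** A reader might infer that the two VFD powers are arithmetically impossible together. The documents do not support that. The powers are simulation output; later data were resampled from the observed baseline cohorts, and baseline VFDs sit in the same model. Holding that baseline fixed is a natural reading, and it steepens the power curve enough to print 87% and 51%. This part of the objection stands.

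It does not go on to defend 87% as the trial's power. Future patients will come from each hospital's underlying distribution, not from the particular baseline sample that happened to be observed. The error in that sample therefore does contribute to Z in the real trial, and a simulation that suppresses it overstates power when mean Z exceeds the critical value.

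On enrolment, a reader might take it as fact that all four powers include excluded patients. The text does not prove this. The three years may simply name a calendar phase, the sample size section ties its 33-month analysis set to the power work, and volume was projected from 2019 levels with 4% growth, so 10,800 is an illustration rather than the article's figure. What stands is that both power sections, as worded, count three years and neither says that the run-in was removed.

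Replicate counts are commonly left to a fuller document, so their absence is not itself the point. The adherence pair shows no comparable anomaly: scaling 86.4% from an odds ratio of 1.333 to 1.4 gives 94.1%, close to the stated 95.4%.

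**Conclusion.** The VFD pair is steeper than a calibrated one-degree-of-freedom test allows, by about 12 to 13 points at one end or the other. This rests on the article's own effect model, with improved patients taken as a random share, and on SD(Z) = 1. A fixed baseline cohort would explain the pair, possibly with some replicate noise. In that case the 87% overstates the planned test's power, which would be about 75% if SD(Z) in the simulation was near 0.6. The article does not say whether the baseline was fixed or redrawn, so neither 64% nor 75% can be put forward as the right value yet.

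The run-in mismatch holds on the wording and is small: 0.4 to 3.4 points for VFD and at most about 2.7 for adherence, all in the optimistic direction if run-in patients were counted. Neither issue affects the validity of the planned tests. Both affect how a null VFD result should be read.

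**What to change.** - Re-run the VFD simulations with 33 months of intervention enrolment, redrawing the baseline cohort in each replicate.
- Use enough replicates for a small Monte Carlo error, and confirm that null rejection is near 5%. Redrawing alone does not guarantee this: null rejection in the stand-in model ranged from 4% to 16%.
- Recompute adherence power on 33 months, or state that the run-in had already been removed.
- Restate 87%, 51%, 86.4% and 95.4% wherever they change, and say briefly how the baseline was handled.

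The cost is a re-run of existing simulation code and a short text change. The downside is somewhat less favourable power figures.

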### Early stopping rules and contingency plan

We will conduct two interim efficacy analyses approximately 12 and 24 months after trial launch to evaluate performance of TEACH intervention versus control. If introduction of the TEACH enhancement plus usual audit and feedback approach leads to substantially greater uptake and adherence during the first part of the study period versus control, such that the benefits of using TEACH far exceed the harms, the DSMB may recommend to stop the clinical trial early, and significant findings will be reported. These interim looks will use prespecified conservative O’Brien-Fleming [63] stopping boundaries, interim looks have only minor effects on effective study power, and early stopping occurs only if nominal statistical significance is substantial. Early stopping for futility is not warranted in our setting, as this trial will provide valuable information on various outcomes and facets of implementation even if adherence rates are ultimately not significantly different.

If the TEACH mechanism demonstrates significantly better adherence to C-SAT/SBT and increased ventilator-free days over the usual audit and feedback approach at an early interim analysis, leading to early stopping of the clinical trial, further actions would be deliberated by the principal investigators and sponsor, with the DSMB having an advisory role. As part of this deliberation, the study principal investigators may propose adjusting or redesigning the existing study, for example, eliminating the sustain measurement in later years and conducting a cost-effectiveness analysis to compare relative implementation performance costs of the TEACH method versus usual audit and feedback approach.

